### Outcome measurement

The primary outcome in this study will be the exclusive breastfeeding rate at month 1, month 3, and month 6 postpartum in both the intervention group and the control group. Secondary outcomes for both intervention group and control group will be as following: 1) the overall duration of any and exclusive breastfeeding across the first 6 months postpartum; 2) mothers’ knowledge on breastfeeding practices; 3) the proportion of early initiation of breastfeeding; 4) the timing of the introduction of solid food to infants.

Exclusive breastfeeding will be defined according to the WHO definition which says that the infant receives breast milk as the only source of food; no other liquids or solids are allowed with the exception of vitamin and mineral supplements or medication [28]. The duration of exclusive breastfeeding is defined as the time in weeks until mothers introduce food or drink except for breast milk (we will ask mothers in the follow-up survey “When did your child first eat or drink other food or liquid except for breast milk, including drinking water?” ).

Any breastfeeding will be defined as the infant receiving any breast milk along with other food or liquids, including formula. The duration of any breastfeeding is defined as the time in weeks until a mother stops breastfeeding completely (we will ask mothers in the follow-up survey “When did you completely stop breastfeeding to your child?”).

Early initiation of breastfeeding will be defined based on the WHO guideline as the infant being put to the mother’s breast within one hour of birth [28].

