### Data collection

Before the intervention, a baseline survey will be carried out via face-to-face interviews to collect data of all participants on demographic characteristics information, antenatal care, as well as breastfeeding knowledge and channels through which they receive information on breasfeeding.

Pregnant women will be asked to come to township hospitals. Those who meet the eligibility criteria will be given full information about the study. After signing the written informed consent, they will be interviewed to collect baseline data. Smartphones will be used to collect data. Two supervisors and 10 interviewers will conduct the baseline survey. Experienced staffs from the Capital Institute of Pediatrics will be the study supervisors, and medical students form Huzhu County Vocational Technical School will be recruited as interviewers. We will conduct one day training for the interviewers, which will include questionnaire explanation, smartphone usage for collecting data, and role play.

Research assistants will be recruited from the Qinghai Institute of Health Sciences to conduct follow-up telephone interviewers at week 1, month 1, month 3 and 6 months postpartum for both the intervention and control group. Follow-up data will be collected on maternal breastfeeding knowledge, practices, reasons for weaning and information channels by smartphones (Additional file 1).

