### Data management and analysis

One research staff member blinded to the treatment allocation will be in charge of database maintenance and management. Logic verification statements will be written in data acquisition software for the smartphone. Baseline data and follow-up data will be saved first on the smartphone, and then wirelessly uploaded into an Excel database via an internet server [29].

Statistical analyses will be performed by the research staff using SAS 9.2 software (SAS Institute, Cary, NC). Continuous variables will be presented as mean and deviation, while categorical variables as numbers and proportions. The homogeneity in baseline characteristics between the intervention group and control group will be estimated using t tests for continuous variables andχ^2^ test for categorical variables. In addition, theχ^2^ test will also be used to compare the differences of exclusive breastfeeding rate between two group at one week, 1 month, 3 months, and 6 months postpartum. Survival analysis will be used to compare the overall duration of any and exclusive breastfeeding between the groups. We will construct Kaplan-Meier survival curves to estimate the median exclusive breastfeeding times and use the log-rank test to compare the differences. We will also perform Cox proportional hazards regression to estimate hazard ratios for stopping exclusive breastfeeding or any breastfeeding.

The principle of intention-to-treat-analysis will be used. This means that participants who drop out or are lost to follow-up during the postpartum period will be considered to have stopped breastfeeding at the point of the last follow-up contact and all randomized participants will be included in the analysis. We will further calculate the odds ratios of any and exclusive breastfeeding at each follow-up time point using logistic regression. All statistical tests will be two-tailed and *P* < 0.05 will be considered significant.

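### The exclusive-breastfeeding duration definition and its interview question omit the supplement and medicine exemption in the plan's own definition, so some infants may be counted as early events in the secondary duration analysis

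*Protocol article*

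**What the plan says.** Three statements in the protocol article, Outcome measurement, bear on this point.

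- **Definition of exclusive breastfeeding.** Breast milk is the only source of food, and "no other liquids or solids are allowed with the exception of vitamin and mineral supplements or medication".
- **Definition of its duration.** The time runs as "the time in weeks until mothers introduce food or drink except for breast milk".
- **Question put to mothers at follow-up.** "When did your child first eat or drink other food or liquid except for breast milk, including drinking water".

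Duration is the first secondary outcome in the same section: "the overall duration of any and exclusive breastfeeding across the first 6 months postpartum". Under Data management and analysis it is treated as a time to event: "We will construct Kaplan-Meier survival curves to estimate the median exclusive breastfeeding times and use the log-rank test to compare the differences". Cox regression for stopping is added. Exclusive-breastfeeding duration also appears in the study aim (end of Background) and in the hypothesis (Discussion).

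The follow-up questionnaire is placed in Additional file 1 (Data collection), which is not shown.

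**The concern.** The first statement exempts supplements and medicines; the second and third do not. The question also points towards a broad reading. It asks about any other liquid and names water as an example, but is silent on the one category that the definition exempts. A mother who gave vitamin drops or a liquid medicine can truthfully give that date.

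The question asks for the first occasion, so a single dose is enough, and nothing that happens later reverses it. What is at stake is whether the duration endpoint measures exclusive breastfeeding as the plan defines it, or a stricter condition that depends on how each mother understands the word liquid. False early events would shorten the estimated medians. If they were equally common in both groups, they would tend to dilute the difference between them.

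**Working it through.** The check is mainly a comparison of texts.

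**Step 1. Set the three statements side by side.** The infants are hypothetical. Each otherwise receives only breast milk up to month 3.

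| Infant receives | Definition of exclusive breastfeeding | Duration definition | Question as worded |
|---|---|---|---|
| Water in week 2 | Ended in week 2 | Ended in week 2 | Ended in week 2 |
| Vitamin drops or medicine syrup in week 2 | Still exclusive at month 3 | Unclear: depends on whether it counts as drink | May be dated to week 2: it is a liquid other than breast milk |
| A crushed tablet in week 2 | Still exclusive at month 3 | Probably not an event | Probably not reported |

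The first row shows that naming water is correct: water does end exclusive breastfeeding under the definition. The conflict lies in the second row.

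**Step 2. Follow the answer into the analysis.** The reported date is the event time for exclusive-breastfeeding duration. In the second row, a week-2 answer produces an event at week 2 for an infant who, under the definition, has had no event by month 3. This error can only bring the date forward.

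**Step 3. Ask which outcomes use the answer.** The article ties the question to duration only. It does not give the item behind the primary rates at months 1, 3 and 6. Those rates may be asked separately with the exemption, or derived from the same answer; the text does not say.

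**Step 4. Ask whether a size can be derived.** A size would need the share of exclusively breastfeeding mothers who would report a supplement or medicine in answer to this question, and when. The documents give neither.

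The only design figure is the 93 per group under Sample size calculation, and it concerns the rate. With p1 = 0.292, p2 = 0.292 + 0.20 = 0.492, mean p = 0.392, two-sided 5% significance and 80% power:

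n = [1.960 × √(2 × 0.392 × 0.608) + 0.842 × √(0.292 × 0.708 + 0.492 × 0.508)]² / 0.20²
= [1.353 + 0.569]² / 0.04
≈ 92.3, rounded up to 93.

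The plan's figure is reproduced. It contains no median, hazard or event count, so it cannot be turned into a loss for the log-rank or Cox analysis.

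**The case against.** The strongest reply has three parts.

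**The term was already defined.** The duration sentence speaks of exclusive breastfeeding immediately after defining it, so the exemption may be meant to carry over. This is a fair reading of the intent. It does not repair the question, because the mother hears the question and not the definition. It also leaves a duration rule that, as written, says something different.

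**Many mothers would not count a dose of medicine as food or drink.** This stands. It is why infants may be misclassified, and why it cannot be said that they will be.

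**The questionnaire is not shown.** Additional file 1 could hold a separate item, a probe or a coding rule. This also stands, and the absence of such detail from an article is not itself a fault. The point rests instead on what the article prints: a duration definition and a verbatim question that do not match the definition beside them. An unseen probe would not remove the mismatch in the printed definition. The training described under Data collection ("We will conduct one day training for the interviewers, which will include questionnaire explanation") does not settle the matter either. It is described for the baseline interviewers, whereas the follow-up calls are made by separately recruited research assistants.

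Three stronger readings are tempting but unsupported.

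- A reader might infer that the primary rates are wrong too. The article does not link this question to them.
- A reader might apply an assumed error to 29.2% and 49.2% at 93 per group and report a loss of power. That calculation concerns the primary rate and not duration, it uses the calculated minimum where 200 per group are to be enrolled, and its error rate would have no source.
- A reader might infer bias between groups, because only the intervention group receives the feeding education and may understand the question differently. That is conjecture; nothing in the documents shows an error that differs by group.

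**Conclusion.** The concern holds in a limited form. The duration definition and the printed question leave out an exemption that the plan's own definition contains. Some infants who meet that definition may therefore be recorded as having stopped early in the Kaplan-Meier, log-rank and Cox analyses of exclusive-breastfeeding duration.

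The direction is known: recorded durations become too short. The size is not known and cannot be worked out from the documents. Dilution of the group difference rests on the assumption that the error is equally common in both groups. The point concerns a secondary outcome, and no effect on the primary rates is shown. It would shrink to a matter of printed wording if Additional file 1 or the coding rules already apply the exemption.

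**What to change.** 1. In the duration definition, add *other than vitamin or mineral supplements or medicine*.
2. Add the same phrase to the follow-up question.
3. Record what the first item was along with its date, so that an exempt item can be recognised and the date of the first non-exempt item used.
4. If Additional file 1 or the coding already does this, say so in the text and align the printed duration definition with it.

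The cost is one phrase in two places and one short item in the telephone interview. It should be done before the first follow-up call, because a bare date collected without the item cannot be corrected afterwards. Design, sample size and analysis methods are unaffected.

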### Sample size calculation

We will calculate the sample size required for this study based on previously collected data in Datong (another county in Qinghai), in which exclusive breastfeeding for 0–6 months children was only 29.2% (unpublished data in 2017). We expect to achieve a 20% increase in the exclusive breastfeeding rate by using the WeChat intervention. With a power of 80 and 5% significance level, we calculate that a sample size of 93 pregnant women respectively for intervention and control group will be sufficient for all the primary and secondary outcomes. To compensate for possible refusal and loss to follow-up, we will enroll 200 pregnant women for intervention and control group, respectively. To achieve this sample size, all eligible pregnant women in the 13 townships will be selected as participants over an estimated period of 15 days.

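### Any breastfeeding has two incompatible definitions, one as a status and one as a duration, and the planned time-point odds ratios do not say which applies

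*Protocol article*

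**What the plan says.** Outcome measurement gives three definitions that bear on this point.

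- Exclusive breastfeeding: breast milk is the only food, and "no other liquids or solids are allowed with the exception of vitamin and mineral supplements or medication".
- Any breastfeeding, as a status: "Any breastfeeding will be defined as the infant receiving any breast milk along with other food or liquids, including formula".
- Any breastfeeding, as a duration: "The duration of any breastfeeding is defined as the time in weeks until a mother stops breastfeeding completely". The follow-up question given for it is "When did you completely stop breastfeeding to your child".

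Data management and analysis uses the term in both forms. For duration it plans Kaplan-Meier curves, a log-rank test and a Cox model: "We will also perform Cox proportional hazards regression to estimate hazard ratios for stopping exclusive breastfeeding or any breastfeeding". For status it plans: "We will further calculate the odds ratios of any and exclusive breastfeeding at each follow-up time point using logistic regression". It does not say how status at a time point is to be derived.

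**The concern.** The status definition joins breast milk to other food or liquids and has no *with or without*. Set beside the definition of exclusive breastfeeding, the two categories do not overlap, so an exclusively breastfed infant would be coded as not receiving any breastfeeding. The duration definition treats the same infant as still breastfed. One term therefore has two meanings within a paragraph.

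This matters because the intervention aims to raise exclusive breastfeeding. Under literal coding, each mother moved from mixed to exclusive feeding changes from yes to no on any breastfeeding. The odds ratio could then suggest harm in a trial that met its target, and could disagree with the hazard ratio for stopping any breastfeeding in the same report.

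**Working it through.** **Inputs**

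- Control exclusive breastfeeding rate E0 = 29.2% (Sample size calculation: "exclusive breastfeeding for 0–6 months children was only 29.2" per cent).
- Planned effect: "We expect to achieve a 20% increase in the exclusive breastfeeding rate by using the WeChat intervention". Read as 20 percentage points, this gives E1 = 49.2%.
- T0 and T1, the shares of control and intervention infants receiving any breast milk at all. The article does not give these. They are assumptions, varied from 60% to 95%.

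**The plan's own figure.** The pooled-variance formula, two-sided 5%, 80% power, mean rate 0.392:

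n = [1.96·√(2·0.392·0.608) + 0.842·√(0.292·0.708 + 0.492·0.508)]² / 0.20² = (1.353 + 0.569)² / 0.04 ≈ 92.4, so 93 per group.

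This matches the stated 93 and confirms the absolute reading of the increase. A relative 20% increase would need 1003 per group. The calculation concerns exclusive breastfeeding only, so the disputed definition does not enter it.

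**Odds ratios under the two meanings**

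- Literal status: proportion = T − E (mixed feeding only).
- Inclusive status: proportion = T.
- OR = [p1/(1 − p1)] / [p0/(1 − p0)], intervention over control.

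For reference, the exclusive breastfeeding OR is (0.492/0.508)/(0.292/0.708) = 2.35.

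Worked case, T = 90% in both arms: the literal proportions are 0.900 − 0.292 = 0.608 (control) and 0.900 − 0.492 = 0.408 (intervention). OR = (0.408/0.592)/(0.608/0.392) = 0.44.

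| T control → intervention | Literal proportions, control v intervention | Literal OR | Inclusive OR |
|---|---|---|---|
| 60% → 60% | 30.8% v 10.8% | 0.27 | 1.00 |
| 70% → 70% | 40.8% v 20.8% | 0.38 | 1.00 |
| 80% → 80% | 50.8% v 30.8% | 0.43 | 1.00 |
| 90% → 90% | 60.8% v 40.8% | 0.44 | 1.00 |
| 95% → 95% | 65.8% v 45.8% | 0.44 | 1.00 |
| 80% → 85% | 50.8% v 35.8% | 0.54 | 1.42 |
| 80% → 90% | 50.8% v 40.8% | 0.67 | 2.25 |
| 60% → 80% | 30.8% v 30.8% | 1.00 | 2.67 |
| 60% → 85% | 30.8% v 35.8% | 1.25 | 3.78 |

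**When the direction reverses.** The literal OR is below 1 exactly when T1 − E1 < T0 − E0, that is, when T rises by less than E. With a planned gain of 20 points in E, the literal OR reaches 1 only if T also rises by 20 points. That is impossible when control T is above 80%.

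**Would it pass for noise?** At T = 90% in both arms with all 200 per arm analysed, z = 0.20/√(2·0.508·0.492/200) = 4.0. With 93 per arm, z = 0.20/√(2·0.508·0.492/93) = 2.7. Either would be nominally significant in the wrong direction.

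**The case against.** The strongest reply is that the inclusive meaning is plainly intended. The term itself says any, the next sentence runs to complete cessation, and the only question quoted for this outcome asks for that date. A hazard of stopping any breastfeeding makes sense from birth only if exclusively breastfed infants are already counted. Dropouts are treated as having stopped breastfeeding at last contact, which fits the same meaning. Status at 1, 3 and 6 months can be read off the cessation date, and coded that way the odds ratio and the survival analysis agree.

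Much of this stands. A reader might infer that the plan commits to an analysis that will point against an effective intervention. The document does not support that, because it contradicts itself and never says that the odds ratios use the literal rule. A reader might also infer that the reversal is automatic. It is not: it needs literal coding and a gain in total breastfeeding smaller than the gain in exclusive breastfeeding. Nor can a single odds ratio be put on it, since T is undocumented. In addition, 29.2% is a rate for children aged 0–6 months, not for any one follow-up.

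The reply does not remove the inconsistency. The one sentence that defines status is the one that fails, and the analysis section does not direct the analyst to the cessation date. Either coding can be defended from the text.

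**Conclusion.** The point holds as an internal contradiction with a conditional consequence. The status and duration definitions of any breastfeeding are incompatible as written, and the time-point odds ratios are not tied to either.

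At the planning rates, with literal coding and equal T, the odds ratio is about 0.27 to 0.44 for assumed T between 60% and 95%, against 1.00 under the inclusive meaning. It remains below 1 for the moderate gains in T shown above. These figures rest on assumed T and on planning rates that are not specific to a time point. They show direction and rough size only.

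The reach is narrow. The time-point odds ratio for any breastfeeding is neither the primary outcome nor a listed secondary outcome. The exclusive breastfeeding comparisons, the sample size and the Kaplan-Meier, log-rank and Cox analyses of duration are unaffected. The wording should still be corrected before analysis, because the two codings can give opposite conclusions from the same data.

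**What to change.** In Outcome measurement, define any breastfeeding as the infant receiving any breast milk, with or without other food or liquids, and say that this includes exclusive breastfeeding. In Data management and analysis, state that the time-point odds ratios use this definition and that status at each follow-up is derived consistently with the duration definition, for example from the reported date of complete cessation.

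The cost is one phrase and one sentence. The cessation date is already collected, so no new data are needed, and neither the sample size nor any other analysis changes.

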### Data collection

Before the intervention, a baseline survey will be carried out via face-to-face interviews to collect data of all participants on demographic characteristics information, antenatal care, as well as breastfeeding knowledge and channels through which they receive information on breasfeeding.

Pregnant women will be asked to come to township hospitals. Those who meet the eligibility criteria will be given full information about the study. After signing the written informed consent, they will be interviewed to collect baseline data. Smartphones will be used to collect data. Two supervisors and 10 interviewers will conduct the baseline survey. Experienced staffs from the Capital Institute of Pediatrics will be the study supervisors, and medical students form Huzhu County Vocational Technical School will be recruited as interviewers. We will conduct one day training for the interviewers, which will include questionnaire explanation, smartphone usage for collecting data, and role play.

Research assistants will be recruited from the Qinghai Institute of Health Sciences to conduct follow-up telephone interviewers at week 1, month 1, month 3 and 6 months postpartum for both the intervention and control group. Follow-up data will be collected on maternal breastfeeding knowledge, practices, reasons for weaning and information channels by smartphones (Additional file 1).

### Data management and analysis

One research staff member blinded to the treatment allocation will be in charge of database maintenance and management. Logic verification statements will be written in data acquisition software for the smartphone. Baseline data and follow-up data will be saved first on the smartphone, and then wirelessly uploaded into an Excel database via an internet server [29].

Statistical analyses will be performed by the research staff using SAS 9.2 software (SAS Institute, Cary, NC). Continuous variables will be presented as mean and deviation, while categorical variables as numbers and proportions. The homogeneity in baseline characteristics between the intervention group and control group will be estimated using t tests for continuous variables andχ^2^ test for categorical variables. In addition, theχ^2^ test will also be used to compare the differences of exclusive breastfeeding rate between two group at one week, 1 month, 3 months, and 6 months postpartum. Survival analysis will be used to compare the overall duration of any and exclusive breastfeeding between the groups. We will construct Kaplan-Meier survival curves to estimate the median exclusive breastfeeding times and use the log-rank test to compare the differences. We will also perform Cox proportional hazards regression to estimate hazard ratios for stopping exclusive breastfeeding or any breastfeeding.

The principle of intention-to-treat-analysis will be used. This means that participants who drop out or are lost to follow-up during the postpartum period will be considered to have stopped breastfeeding at the point of the last follow-up contact and all randomized participants will be included in the analysis. We will further calculate the odds ratios of any and exclusive breastfeeding at each follow-up time point using logistic regression. All statistical tests will be two-tailed and *P* < 0.05 will be considered significant.

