A **rewards component** will also be developed to stimulate mothers to participate in our study. During the intervention, mothers can receive scores as long as they participate in WeChat activities. Different types of activities will result in different scores (Table 2). We will rank the scores mothers receive every month, and the top 10 WeChat active mothers will be given rewards, such as toys, picture books, or children towels.

**Table 2 Tab2:** Scores received from activities

Activities	Scores (points)
Registration	20
Read and review the breastfeeding messages in the feeding lecture classroom	5 per message
Share learning experience	2 per message
Score the feeding messages	1 per message
Feeding knowledge competition	2 per time
Questionnaires	20 per time
Baby growth chart	2 per time

The “ke Xue Wei Yang (Optimal feeding)” module was pre-tested in Huzhu County in Aug 2018. Semi-structured interviews were conducted among 17 pregnant women in their second or third trimester and 16 mothers who had a child aged 0–6 months to learn their use experience of the platform to learn from their experience in using the platform. They generally accepted the platform, as they thought the information was easy to understand and useful. They also suggested that both videos and text&picture should be delivered to mothers, as some mothers like video, while some like text&pictures. The detailed description of the methods and results of the pre-test will be reported elsewhere (manuscript in preparation).

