### Control group

Mothers in the control group will only receive the routine antenatal and postnatal health care services (as will the intervention group). Participating infants in both groups will receive routine physical checkups (1, 3, 6, 9 and 12 months) in their own village clinics during their first year [7]. Although participants in the control group will also follow the “Huzhu County Maternal and Child Health Family Planning Service Centre” WeChat official account, they cannot log in the “ke Xue Wei Yang (Optimal feeding)” module and get feeding information from the module.

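### Treating every woman lost to follow-up as having stopped breastfeeding at her last contact biases the rates and the durations, and turns unequal loss into a false group difference if loss is unrelated to feeding

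*Protocol article*

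**What the plan says.** Data management and analysis sets one rule for missing follow-up and presents it as the meaning of intention-to-treat. It covers drop-outs and women "lost to follow-up during the postpartum period will be considered to have stopped breastfeeding at the point of the last follow-up contact". The analysis set is fixed in the same sentence: "all randomized participants will be included in the analysis". No other handling is stated. The same section lists the chi-square comparisons at each visit, the Kaplan-Meier curves, the log-rank test, the Cox models and the logistic regressions.

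The rule thus reaches the main result. Under Outcome measurement, "The primary outcome in this study will be the exclusive breastfeeding rate at month 1, month 3, and month 6 postpartum". Durations of exclusive and of any breastfeeding are secondary outcomes. The second of these ends only when the mother stops breastfeeding altogether.

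Two other places bear on whether loss could differ between arms. The Intervention section describes a rewards component that "will also be developed to stimulate mothers to participate in our study". Table 2 gives 20 points per questionnaire. The Control group section says of the feeding module that controls follow the same official account but "they cannot log in the" module.

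**The concern.** Intention-to-treat means analysing women in the group to which they were randomized. It does not require an outcome to be assigned to a woman whose outcome is unknown. Three consequences follow.

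- **Survival analyses.** A mother who reports EBF at month 1 and then cannot be reached is entered as having stopped at month 1, the date on which her own report says the opposite. For any breastfeeding, a missed call becomes complete weaning. Estimated durations are shortened in both arms.
- **Visit rates, equal loss.** Lost women stay in the denominator as failures, so a true difference shrinks.
- **Visit rates, unequal loss.** The arm that loses more women looks worse even if feeding is identical. The rule is often thought conservative, but it is so only if the intervention arm loses at least as many women as the control arm.

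At stake is whether a difference in the primary outcome or in the hazard ratios reflects feeding or ease of contact.

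**Working it through.** **Inputs from the article.** Sample size calculation: "exclusive breastfeeding for 0–6 months children was only 29.2"% (in another county of the province); "We expect to achieve a 20% increase in the exclusive breastfeeding rate"; "With a power of 80 and 5% significance level"; 93 per arm calculated, 200 per arm enrolled. Tests are two-tailed.

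**Inputs assumed.** Loss by arm, because none is given: mainly 5% (intervention) v 15% (control), with other values for range. EBF of 40% and 50% are also assumed, because 29.2% covers ages 0-6 months and early visits may run higher.

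**Step 1. Reproduce the article's figure.** Reading the 20% as percentage points (29.2% to 49.2%, mean 39.2%):

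n = [1.960 × √(2 × 0.392 × 0.608) + 0.842 × √(0.292 × 0.708 + 0.492 × 0.508)]² / 0.20² = 92.3, rounded up to 93.

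This matches. Enrolling 200 leaves room for 1 − 93/200 = 53.5% refusal plus loss, so the article itself allows for substantial attrition.

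**Step 2. Equal loss.** If a proportion d is lost in both arms, the difference becomes 20 × (1 − d) points. At d = 20% it is 16 points.

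**Step 3. Unequal loss, no true effect, loss unrelated to feeding.** Each arm's analysed rate is p × (1 − d), so the false difference is p × (control loss − intervention loss). For p = 29.2% and loss of 5% v 15%:

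- intervention 0.292 × 0.95 = 27.7%; control 0.292 × 0.85 = 24.8%; difference 2.9 points
- standard error √(2 × 0.2628 × 0.7372 / 200) = 0.0440
- probability of significance in favour of the intervention: Φ[(0.0292 − 1.96 × 0.0440)/0.0440] = Φ(−1.30) = 9.7%; adding 0.4% in the other direction gives 10.2%

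| True EBF in both arms | Loss 5% v 15%: false difference | Rejection | Loss 5% v 25%: false difference | Rejection |
|---|---|---|---|---|
| 29.2% | 2.9 points | 10.2% | 5.8 points | 27% |
| 40% | 4.0 points | 13% | 8.0 points | 39% |
| 50% | 5.0 points | 17% | 10.0 points | 53% |

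With equal loss the rejection rate is 5.0%. With the arms' loss rates swapped, the same excess runs against the intervention.

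**Step 4. Log-rank under the null, by simulation.** 200 per arm, exponential EBF durations (29.2% still exclusive at 26 weeks, or medians of 12 or 20 weeks), and last contact of lost women equally likely at week 1, month 1 or month 3, regardless of feeding. At 5% v 15% loss, separate runs give rejection of about 13-20% when loss counts as stopping and about 5-6% when it is censored. At 5% v 25% the rule rejects about 40-60%, and censoring stays near 5%.

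**Step 5. The opposite assumption.** Now suppose that only mothers who have already stopped are lost. At 5% v 15% the article's rule rejects about 5-6%. Censoring rejects about 8-25%, against the intervention, depending on whether loss is counted as a share of those who stop or of all women. At 5% v 25% censoring rejects roughly 30-77%.

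**The case against.** The strongest reply is Step 5. The rule assumes that loss signals stopping. If that is true, the rule is close to correct and censoring is the biased choice. The article does not show which assumption holds. This stands: a reader might infer that censoring removes the problem, but it does so only if loss is unrelated to feeding given what is known. It is a reason to report both approaches, not to make the more extreme one the sole analysis.

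A reader might also infer that the plan pays only the intervention arm to answer the outcome interviews, and so builds in the imbalance. The article does not support this. Outcomes come from telephone interviews by research assistants in both arms (Data collection). Table 2 does not say that its questionnaires are those interviews, and points are tied to WeChat activities. Prizes go to the top 10 each month, about 5% of 200 women. No sentence says that controls receive nothing. Both arms add an Assistant account for follow-up, and eligibility leaves out women who plan to change their number or be away long-term. What remains is that only intervention mothers have access to the module, so better contact with them is plausible. They might equally tire of the messages and drop out more.

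Finally, an analysis plan that is not shown may hold sensitivity analyses, and may say how to handle a woman last contacted before delivery. Neither absence is counted here. The point is the rule that the article does fix.

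**Conclusion.** The concern holds as a fault in the stated missing-data rule. Applied as written, the rule can contradict a mother's last report, shortens durations, dilutes a true effect under equal loss (20 points becomes 16 at 20% loss), and converts unequal loss that is unrelated to feeding into a false difference. At an assumed 5% v 15% loss with no true effect, the nominal 5% error becomes about 10% at the article's own 29.2%, 13% at 40% and 17% at 50%, and about 13-20% for the log-rank test.

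These sizes rest on assumed loss rates and on loss unrelated to feeding. The false difference at 29.2% is 2.9 points, small beside the planned 20, so the rule would not by itself produce the planned effect. Neither unequal loss nor its direction is established. The conclusion is therefore not that the trial will favour the intervention, but that its main analyses are open to a bias that can be largely avoided if loss depends only on observed data.

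**What to change.** In Data management and analysis:

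1. Define intention-to-treat as analysis by randomized group, separately from the handling of missing data.
2. In the Kaplan-Meier, log-rank and Cox analyses, censor at the last contact with known feeding status.
3. For EBF at months 1, 3 and 6, use multiple imputation or a likelihood-based model that draws on earlier contacts and baseline data.
4. Keep the present rule as a named sensitivity analysis, because censoring is itself biased if loss signals stopping.
5. Report loss by arm at each contact.

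The points table need not change, since its link to the outcome interviews is not shown. The cost is some extra programming and reporting, and a primary analysis that relies on data being missing at random, which the sensitivity analysis then tests. Design, sample size and data collection stay as they are.
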